Children are required to discontinue regular PT interventions prior to the first baseline assessment and to abstain from starting any other PT during the trial to reduce the chance of confounding effects associated with any previous or concurrent treatment. The child is allowed to continue any existing program of soft tissue stretches and/or basic walking and standing, but their clinical physiotherapist (PT), or other clinician, is asked not to alter the programs during the course of the study. Activities are monitored at the start of each intervention session (Lokomat or PT), when the child and parent are asked by the study PT about any other gross motor-based treatments and physical activity they did since the last session. These physical activity descriptions are documented in the child’s session log. The study PT is required to alert the research assistant (RA) to any potential co-interventions. Subsequently, the RA calls the parent to ask them to put any activities on hold that are judged to be walking-related co-interventions.

During the six-week break that occurs before crossing to the other intervention arm, the child is allowed to continue their existing regimen of soft tissue stretches and any basic walking/standing home program they had been given prior to the trial, but asked not to embark on any other new therapy. The RA phones the parent mid-way through this phase to check for any treatments that the child may have started/resumed. A request to discontinue any added treatment may be made by the RA after discussion with the co-Principal Investigators (co-PIs) if it appears to be a gait-related co-intervention (i.e., a possible confounder). While the six weeks between the two intervention arms is not a true wash-out period (since effects of rehabilitation are not expected to be reversible when therapy is withheld), it does give a time break for families between the two phases. A new baseline is established before starting the second intervention to ensure intervention effects are isolated for analysis (Mayr et al. 2007).

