## Analyses

Data entry forms were built for each measure in the study to correspond to the paper forms that the assessors used. REDCap (Harris 2012) requires outer limits for each value, and each paper data sheet is double entered for purposes of data verification process. Collectively these features optimize the data entry accuracy. Study data will be kept for seven years following conclusion of the trial, at which point data will be destroyed following REB requirements.

Descriptive statistics and graphic displays will be presented for all outcomes for the PT and Lokomat interventions (pre, post-test and change scores). Equivalence between baseline_A_ and baseline_B_ scores will be evaluated for each outcome; a t-test or Wilcoxon test will be used in this comparison as appropriate. The primary analysis will be for the pre- to post-test differences (change scores) of the GMFM-66 and 6MWT between groups. Assuming normality of data, a repeated measures ANCOVA will be performed on GMFM-66 and 6MWT change scores to compare the effects of the Lokomat and gait-related PT interventions. The child’s relevant baseline score (baseline_A_/baseline_B_) will be used in the ANCOVA to increase analytic precision. The P value will be adjusted to 0.025 to handle the expected high correlation between the GMFM-66 and timed walk. Evaluation of an intervention order effect (i.e., being the first or second treatment), as well as the interactions with intervention group will be built into this analysis (Senn 2002). Secondary sub-analyses will be done in the same way within GMFCS II and III subgroups to determine any differential response for GMFCS Level.

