Due to the lack of expectation of return to baseline in the break period, a second analytic approach will be taken as well using a generalized estimating equation (GEE) adjustment for repeated measures within subjects analysis (Baker et al. 2007). In this approach treatment effects are evaluated via regression analysis and the GEE method will allow the fit of two models. The first is for treatment effect, treatment-period effect, and differential carryover effect adjusting for the baseline scores, and the second is treatment effect and treatment-period effect with exclusion of any differential carryover effect. Factors hypothesized a priori to be associated with GMFM-66 change score magnitude will be entered within this model using a forward stepwise regression procedure, e.g., age, GMFCS Level, motivation (DMQ) score, ASK baseline score.

Finally, a third approach will be taken if there is significant evidence of a carryover effect and significant interaction effects. This will be to focus on the data from the first arm of the study, i.e., an ANCOVA adjusted for baseline GMFM-66 change scores of just the first intervention period (randomisation to either Lokomat or PT with 20 children per group). This comparison in itself would have a power of about 0.60 for the GMFM-66 (with alpha = 0.025 and a medium effect size of 0.50).

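### The first-period-only analysis is triggered by a carryover test that uses the same data, at an unadjusted 0.025; if its result can stand in for the primary one, the false-positive rate rises modestly

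*Protocol article*

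**What the plan says.** All of the following is in the protocol article. The Analyses section makes a repeated measures ANCOVA of change scores primary for the two co-primary outcomes, GMFM-66 and the 6-minute walk test. On the significance level it says: "The P value will be adjusted to 0.025 to handle the expected high correlation between the GMFM-66 and timed walk". The same model is to include "Evaluation of an intervention order effect (i.e., being the first or second treatment), as well as the interactions with intervention group".

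A second approach is a GEE fitted twice, once with a differential carryover term and once without; of the latter it says "the second is treatment effect and treatment-period effect with exclusion of any differential carryover effect".

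Then comes the conditional step: "Finally, a third approach will be taken if there is significant evidence of a carryover effect and significant interaction effects". It is an ANCOVA of the first period only, described as "randomisation to either Lokomat or PT with 20 children per group", with "power of about 0.60 for the GMFM-66 (with alpha = 0.025 and a medium effect size of 0.50".

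No significance level is given for the carryover or interaction test. Nothing adjusts the 0.025 for the switch. The Design section says that the six-week break is not a true wash-out, because "effects of rehabilitation are not expected to be reversible when therapy is withheld", and that a new baseline is taken before the second intervention.

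**The concern.** Testing for carryover and then moving to first-period data is a two-stage procedure on one data set. The carryover test compares the two sequences on the sum of both periods' changes, and the fallback compares the same two groups on the first of those changes. A chance imbalance in period 1 therefore tends to trigger the fallback and also to make it significant. If the conclusion on a co-primary outcome can then rest on the fallback, the stated 0.025 is not the error rate of the procedure.

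The trigger is also a between-child comparison in a small trial, so it will often miss real carryover, and its silence may be read as reassurance. Asking for both carryover and interaction looks like two safeguards but is close to one.

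**Working it through.** **The plan's own figure for the fallback.** Inputs (Analyses): 20 per group, standardised effect 0.50, alpha 0.025. The noncentrality is 0.50 × √(20/2) = 1.58 on 38 degrees of freedom. Power is 0.34 one-sided or 0.24 two-sided, not 0.60. An ANCOVA would reach 0.60 only with a covariate correlation of about 0.70 (one-sided) or 0.77 (two-sided), which is not stated. This is a side observation; the point below does not depend on it.

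**Carryover and interaction.** Two sequences by two periods give four cell means. After the overall mean, the period effect and the treatment effect, one contrast is left. It is at once the sequence effect, the order-by-intervention interaction and differential carryover. The ANCOVA and the GEE may estimate it slightly differently, but they do not supply two independent pieces of evidence.

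**Correlation of the pre-test with the fallback.** Let c1 and c2 be a child's two change scores, with equal variance σ² and correlation ρ.
- Cov(c1, c1+c2) = σ²(1+ρ) and Var(c1+c2) = 2σ²(1+ρ).
- Hence corr = (1+ρ)/√(2(1+ρ)) = √((1+ρ)/2), which is 0.71 at ρ = 0 and 0.87 at ρ = 0.5.
- The cross-over test uses c1−c2, which is uncorrelated with c1+c2.

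**Error of the two-stage rule,** with no treatment effect and no carryover. Let a be the carryover test level and J the bivariate normal probability that both the carryover test and the first-period test (two-sided 0.025) reject. Overall error = (1−a) × 0.025 + J; error once the fallback is entered = J/a. The values of a and ρ are assumptions.

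| a | ρ | J | Overall error | Error given fallback |
|---|---|---|---|---|
| 0.025 | 0 | 0.0072 | 0.032 | 29% |
| 0.025 | 0.5 | 0.0122 | 0.037 | 49% |
| 0.05 | 0 | 0.0107 | 0.034 | 21% |
| 0.05 | 0.5 | 0.0171 | 0.041 | 34% |
| 0.10 | 0 | 0.0149 | 0.037 | 15% |
| 0.10 | 0.5 | 0.0214 | 0.044 | 21% |

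Example, third row: 0.95 × 0.025 + 0.0107 = 0.034.

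**With baseline adjustment,** as the plan specifies (simulation, 20 per sequence, 20,000 trials per setting, carryover level 0.025–0.10): overall error is 0.030–0.038 when the four assessments are equally correlated, and 0.028–0.030 when correlation decays over time. At carryover level 0.05–0.10, error given the fallback is about 16–22% and 6–12% respectively. The cross-over test used without any switch gives 0.023–0.028. Simulation error is about √(0.025 × 0.975/20,000) = 0.001, so under decaying correlation the excess is small.

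**Power of the carryover test** for a differential carryover of 3 points (assumed, equal to the target treatment difference in Sample size), by noncentral t. The plan's SD of 6 can be read in two ways:
- as the SD of one change score, so the SD of the sum is 6√(2(1+ρ));
- as the SD of the within-child difference, so the SD of the sum is 6√((1+ρ)/(1−ρ)).

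The lowest power is with 16 per sequence, ρ = 0.5, level 0.05. The SD of the sum is 10.39 on either reading, SE = 10.39 × √(2/16) = 3.67, noncentrality 0.82, power 0.12. The highest is on the second reading with 20 per sequence, ρ = 0, level 0.10: SD 6, SE = 6 × √(2/20) = 1.90, noncentrality 1.58, power 0.46. Other combinations fall between.

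**The case against.** The strongest reply is that the primary analysis is fixed without condition and the third approach is only an addition. The text has the analysis turn its focus to first-period data; it nowhere says that the primary ANCOVA is withdrawn or that the conclusion moves. A reader might infer outright replacement, but the document does not say so. If the fallback is merely supportive, the primary test stays at 0.025 and the defect is an unclear hierarchy. That stands, and the inflation is conditional on it.

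Four further points also stand.
- The inflation is modest and baseline adjustment reduces it. At carryover levels of 0.05–0.10, a trial with no true carryover enters the fallback only 5–10% of the time. If 0.025 is one-sided, the overall error at carryover level 0.05 is 0.032–0.037.
- A reader might infer that naming one contrast twice makes the fallback easier to reach. It cannot: requiring both is redundant or slightly stricter.
- A reader might take the statement that rehabilitation effects are not reversible as proof of differential carryover. The new baseline before period 2 absorbs persistent gains, so the statement does not show differential carryover in change scores.
- Carryover power of 12–16% follows from one reading of SD 6, 16 per sequence and level 0.05; it is the low end of the range.

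None of this removes the correlation between trigger and fallback, or supplies a level for the trigger.

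**Conclusion.** The point holds in a limited form. The plan selects the first-period analysis by a test that shares its data, and gives it the full 0.025. If that result replaces or competes with the primary one, overall error is about 0.03–0.044, and nearer 0.028–0.038 with baseline adjustment. Error within the fallback is about 15–34% at carryover level 0.05–0.10 before baseline adjustment, and lower with it. All of this rests on assumed carryover levels and an assumed ρ of 0–0.5.

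Carryover power of roughly 12–46% for 3 points means that a non-significant result does not show carryover to be absent. The double condition adds little protection. This should be fixed. It is not a fatal flaw, because the inflation is modest and depends on a reading that the text leaves open.

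**What to change.** Remove the conditional trigger. State that the within-child cross-over ANCOVA remains the primary analysis of both co-primary outcomes whatever the carryover test shows. Always report the first-period contrast and the sequence (carryover) contrast, each with a confidence interval, as supportive results, and say that carryover and order-by-intervention interaction are essentially one contrast in this design.

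The cost is wording only; no data, visits or children are added. The downside is that a real differential carryover would bias the primary estimate by up to half its size, for example 1.5 points for a carryover of 3. The first-period estimate, reported every time, would let readers see this, though imprecisely at 20 per group.

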### Randomisation

Children who meet the eligibility criteria and pass the screening assessment are assigned a study ID number, and then attend their baseline assessment. Following the baseline assessment, the child is allocated to start in either the Lokomat or PT intervention phase via a process of random assignment using a computer generated random numbers system. The assignment scheme was prepared at the start of the study by a non-study RA, using a stratified randomisation process (age and GMFCS level) that employed mixed allocation blocks of 4 and 6 children. By the end of the trial, this system will ensure that the number and age/GMFCS balance of participants who start in the Lokomat and PT intervention groups will be even. Management of the randomisation process by a non-study RA through the entire study allows the study investigators to remain blinded to the scheme, thereby eliminating allocation bias. Participants are informed of the intervention order by the study RA.

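### Age and GMFCS level stratify the randomisation but are not named as covariates in the first-period ANCOVA or the order-by-intervention ANCOVA, so these between-child tests are conservative to the extent that the strata predict change beyond baseline.

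*Protocol article*

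**What the plan says.** All places are in the protocol article.

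- **Randomisation.** The allocation list was prepared "using a stratified randomisation process (age and GMFCS level) that employed mixed allocation blocks of 4 and 6 children".
- **Analyses, repeated measures ANCOVA.** The one covariate named is the child's relevant baseline score, which "will be used in the ANCOVA to increase analytic precision". The order effect is examined in the same model: "Evaluation of an intervention order effect (i.e., being the first or second treatment), as well as the interactions with intervention group" are to be part of it.
- **Analyses, GEE.** The first of two models includes a "differential carryover effect adjusting for the baseline scores". Further predictors, described as "Factors hypothesized a priori to be associated with GMFM-66 change score magnitude", are to be "entered within this model using a forward stepwise regression procedure, e.g., age, GMFCS Level, motivation (DMQ) score, ASK baseline score".
- **Analyses, first-period fallback.** If carryover and interaction are both significant, the plan turns to "an ANCOVA adjusted for baseline GMFM-66 change scores of just the first intervention period", with 20 children per group. It gives the power as about 0.60 at alpha 0.025 and an effect size of 0.50.
- **Analyses, subgroups.** The primary models are repeated within GMFCS II and within GMFCS III.

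**The concern.** In a two-period cross-over the Lokomat–PT contrast is made within the child, so a stable effect of age or GMFCS level on change cancels. Two other comparisons are made between children. One is the first-period comparison. The other is the order-by-intervention term, which with two periods and two sequences is the same contrast as the sequence (carryover) effect.

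For such comparisons, blocking within strata balances the strata across groups and so removes their variation from the sampling error of the estimate. A model without the strata still counts that variation as residual error. If the strata are prognostic, the reported standard error is then larger than the true one and the test rejects too rarely. The plan itself expects both factors to be associated with change, yet makes them candidates in one model only, and there only by data-driven entry.

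What is at stake is precision in two comparisons that are already weak. A conservative carryover or interaction test is also less likely to trigger the fallback meant to deal with carryover.

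**Working it through.** **Inputs from the protocol article.** 20 children per group, effect size d = 0.50, alpha 0.025 with sidedness not stated, stated first-period power about 0.60 (Analyses). Cross-over difference 3 points, SD 6, power 0.80, n = 32 (Sample size).

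**Assumed input.** R², the share of residual variance of change that age and GMFCS level explain beyond baseline. The article gives no value; 0, 0.10 and 0.20 are used.

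**1. Which sidedness does the plan use?** Paired normal formula: n = ((z_alpha + z_power) / (3/6))².
- One-sided 0.025: ((1.960 + 0.842)/0.5)² = 31.4, so 32, as stated.
- Two-sided 0.025: ((2.241 + 0.842)/0.5)² = 38.0, which rounds up to 39.

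The stated 32 matches the one-sided reading. Both are carried forward.

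**2. The plan's first-period power.** Noncentrality = d × √(n/2) = 0.5 × √10 = 1.581.
- Noncentral t, 38 df: 0.338 one-sided, 0.238 two-sided.
- Normal approximation: 0.352 one-sided, 0.255 two-sided.

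The stated 0.60 is not reproduced. About 0.60 appears with 40 per group (0.598 by t, one-sided), with the paired normal formula on 20 children (0.609), or if baseline alone explained about 52% of the variance (one-sided).

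**3. Size of the standard error excess.** Under stratified allocation, unadjusted SE / true SE ≈ 1/√(1 − R²).
- R² = 0: 1.00
- R² = 0.10: 1/√0.90 = 1.054, about 5% too large
- R² = 0.20: 1/√0.80 = 1.118, about 12% too large

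**4. First-period power with the strata in the model.** Noncentrality = 1.581/√(1 − R²). Degrees of freedom fall from 37 (baseline only) to 35. No gain from baseline is credited.

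| Model | Noncentrality | Two-sided 0.025 | One-sided 0.025 |
|---|---|---|---|
| Baseline only, 37 df | 1.581 | 0.238 | 0.337 |
| Strata added, R² = 0, 35 df | 1.581 | 0.237 | 0.336 |
| Strata added, R² = 0.10, 35 df | 1.667 | 0.263 | 0.367 |
| Strata added, R² = 0.20, 35 df | 1.768 | 0.296 | 0.405 |

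**5. Check by simulation.** 40 children, 2 × 2 strata, blocks of 4 and 6, 6,000 runs per setting, two-sided 0.025, ANCOVA on baseline without the strata:

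| Assumed setting | Model SE | Empirical SD | Type I error |
|---|---|---|---|
| Strata not prognostic | 0.319 | 0.321 | 0.025 |
| Strata explain 10% (5% each) | 0.320 | 0.308 | 0.019 |
| Strata explain 20% (10% each) | 0.321 | 0.290 | 0.013 |
| GMFCS alone 20%, baseline 2 SD apart between levels | 0.301 | 0.294 | 0.019 |
| GMFCS alone 20%, baseline 3 SD apart | 0.294 | 0.290 | 0.024 |

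The excess is about 4% and 11% in the second and third rows, close to step 3. It is only about 1–2% in the last two, because baseline GMFM-66 already carries most of what GMFCS level would add. With age alone explaining 20%, it stays at about 10–12%. There was no appreciable bias in any setting.

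**The case against.** **The article does not say that only baseline is used.** It is a condensed document, and a full covariate list may stand in an analysis plan that is not shown. A reader might infer that the strata are deliberately excluded; the text does not support that. What stands is that the article does name covariates for each model, and where it brings in age and GMFCS level it leaves them to stepwise entry.

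**The strata are not absent from the carryover question.** The GEE tests differential carryover and can take in both factors, and the subgroup analyses remove GMFCS level by restriction. This is correct and narrows the point. But forward selection may drop a design factor on the evidence of the data, and the GEE changes neither the first-period ANCOVA nor the interaction test in the repeated measures ANCOVA.

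**The excess is conditional.** A reader might infer that these standard errors are simply too large. They are not if the strata add nothing beyond baseline, and the part due to GMFCS level is probably small. This objection stands in full, and the point is worded accordingly.

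**Little hangs on it.** A reader might also infer that these tests decide how the trial is read. The primary analysis is the within-child contrast, which is unaffected. The fallback runs only after significant carryover and interaction, the error is conservative, and power stays low after the fix. This objection stands too and limits the point to a minor improvement.

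**Conclusion.** The point holds in its conditional form and is minor. Two between-child analyses name baseline alone as covariate although allocation is stratified on two factors that the plan expects to be associated with change. Their standard errors are too large by about 5% or 12% if the strata explain 10% or 20% of residual variance, and by nothing if they explain none. Those shares are assumptions. Age is the main exposure, on the further assumption that baseline GMFM-66 differs strongly between GMFCS levels.

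The power gain in the first-period comparison is 0.03 to 0.06 two-sided and 0.03 to 0.07 one-sided, with no credit for baseline. If baseline explains much of the variance, all the power figures are higher. Stratum adjustment at these shares does not bridge the gap to the stated 0.60, which needs its own explanation.

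**What to change.** State that GMFCS level and age (as stratified, or continuous) enter as prespecified fixed covariates, next to the baseline score, in:

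- the first-period ANCOVA;
- the repeated measures ANCOVA that tests order and order-by-intervention;
- the GEE model that tests differential carryover, with both factors forced in and stepwise selection kept, if at all, for the remaining candidates.

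The cost is a sentence of analysis wording and about 2 degrees of freedom. Both variables are known at randomisation. If the strata turn out not to be prognostic, first-period power changes by about 0.001 (0.238 to 0.237 two-sided, 0.337 to 0.336 one-sided).

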## Study aims and hypothesis

The primary aim of the study is to determine the impact on gait-related gross motor skills of a gait training program using a robotic-assisted gait trainer (the Lokomat^®^Pro) compared with a gait-related physiotherapy (PT) program for children in GMFCS Levels II and III. The primary hypothesis is that children receiving the Lokomat intervention will improve more on the GMFM-66 and 6-minute walk test (6MWT) than those in the gait-related PT program.

The secondary objective is to evaluate the comparative impact of Lokomat training and gait-related PT on: (a) individualized walking/gross motor based goals; (b) the amount/location of walking the child does each day (environmental context and season considered); (c) participation in activities and (d) health-related quality of life.

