## Sample size

The study has been designed and powered to ensure adequate sample size for the primary research questions and analysis of children in GMFCS Levels II and III. The starting point for our sample size calculation consideration was a single group Lokomat study with a similar GMFCS sample and Lokomat use protocol in which the GMFM Stand and Walk mean scores changed by approximately 5 points (SD change = 7) (Borggraefe et al. 2010b). Our study is powered to let us detect a difference between the two interventions of three points (SD = 6: small effect size) on the GMFM-66, a magnitude of change that is considered to be a minimally clinically important difference (Oeffinger et al. 2008) when evaluating benefits of treatment. The reason for a difference change target in our study is that we are comparing two active interventions, each of which could result in positive change given the walking focus and boost for many of the children in therapy intensity. This sample size is also sufficient to handle the 6MWT comparisons and the small effect size observed by others in single group Lokomat studies in the 6MWT results (mean gains of 25 m [SD = 50 m], personal communication, Glenrose Hospital program, 2012).

For crossover designs, sample size calculations that link with a matched pairs *t* test calculation are appropriate (Senn 2002). A paired *t* test is also the underlying basis for the more sensitive repeated measures ANOVA that we have chosen to use so that we can include a period effect within the analysis. With an alpha of 0.025, beta of 0.20, and a detectable change score difference between intervention of thre points on the GMFM-66 (with an estimated SD of change of 6.0 points), a sample of 32 children is required (Hintze 2001). We increased the sample requirement to 40 to account for a potential drop out/protocol deviation rate of 20%. Sample calculation based on this generous drop-out rate will support the primary efficacy analysis that focuses only on the children who attend more than 70% of the sessions within one or the other intervention phase.

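### The stated power of about 0.60 for the first-period-only GMFM-66 comparison does not follow from its own inputs, which give about 0.24 (two-sided) or 0.34 (one-sided)

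*Protocol article*

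**What the plan says.** The Analyses section sets out three approaches for the GMFM-66. The third applies if there is significant evidence of carryover together with significant interaction effects. It is described as "an ANCOVA adjusted for baseline GMFM-66 change scores of just the first intervention period", with "randomisation to either Lokomat or PT with 20 children per group". The article says that this comparison "would have a power of about 0.60 for the GMFM-66 (with alpha = 0.025 and a medium effect size of 0.50").

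The other relevant statements are:

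- **Alpha (Analyses).** "The P value will be adjusted to 0.025 to handle the expected high correlation between the GMFM-66 and timed walk". Nothing says whether 0.025 is one-sided or two-sided.
- **Hypothesis (Study aims and hypothesis).** It is directional: "children receiving the Lokomat intervention will improve more on the GMFM-66 and 6-minute walk test (6MWT").
- **Sample size.** For the paired cross-over comparison the target is a difference of three "points on the GMFM-66 (with an estimated SD of change of 6.0 points), a sample of 32 children is required", with beta 0.20. This is raised to 40 for 20% drop-out or protocol deviation.
- **Label.** The same ratio of 3 to 6 is called small in Sample size ("SD = 6: small effect size) on the GMFM-66") and medium in Analyses ("a medium effect size of 0.50").

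**The concern.** Group size, effect size and alpha all stand beside the stated power, so the figure can be checked directly, and it looks too high. A cross-over of 32 children was sized for 80% power at this same ratio because each child serves as his or her own control. Two independent groups of 20 lose that advantage, and a fall only to 60% is hard to credit.

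What is at stake is how a first-period result would be read. If this analysis were triggered, a reader relying on 0.60 would think that an effect of the assumed size had a 40% chance of being missed. If the true chance is well above half, a non-significant result carries little information and could be mistaken for evidence that the two therapies do not differ.

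**Working it through.** **Inputs.** n = 20 per group, d = 0.50 and alpha = 0.025 (Analyses). d agrees with 3/6 = 0.50 from Sample size, where 6 is described as an SD of change. Sidedness and baseline correlation are not given, so both sides and a range of correlations are shown.

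**1. Which sidedness does the article's own sample size imply?** For a paired comparison by normal approximation, N = (z_alpha + z_beta)² / d², with z_beta = 0.842 for 80% power.

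- One-sided 0.025: (1.960 + 0.842)² / 0.25 = 31.4, so 32. This is the article's figure. The exact t calculation gives 34.
- Two-sided 0.025: (2.241 + 0.842)² / 0.25 = 38.0, so 39. The exact t calculation gives 41.

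Of these two readings of 0.025, only the one-sided one, by normal approximation, reproduces 32. Numerically it is the same as two-sided 0.05.

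**2. First-period power without covariate gain.** Noncentrality = d × √(n/2) = 0.50 × √10 = 1.581, with 38 degrees of freedom.

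| Alpha | Critical t | Power (noncentral t) | Power (normal approximation) |
|---|---|---|---|
| two-sided 0.025 | 2.334 | 0.238 | 0.254 |
| one-sided 0.025 | 2.024 | 0.338 | 0.352 |

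A simulation of 200,000 trials for the two-sided case gave 0.240. Even a one-sided alpha of 0.05, looser than the article states, gives only 0.463.

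**3. What baseline adjustment could add.** If baseline correlates with the analysed change score at r, the effective d becomes 0.50 / √(1 − r²), and one degree of freedom is lost.

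| r | Two-sided 0.025 | One-sided 0.025 |
|---|---|---|
| 0.3 | 0.26 | 0.36 |
| 0.5 | 0.32 | 0.43 |
| 0.7 | 0.46 | 0.58 |
| 0.8 | 0.62 | 0.73 |

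Power of 0.60 needs an effective d of about 0.82 (two-sided) or 0.72 (one-sided). Solving r = √(1 − (0.50/d)²) gives r of about 0.79 or 0.72.

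**4. Group size needed for 0.60 at d = 0.50, unadjusted.** 52 per group (two-sided) or 41 (one-sided).

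**5. A possible origin.** With 40 per group, one-sided 0.025 gives 0.598. The total of 40 may have been entered as the size of each group. This is an inference; the article does not show its calculation.

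**6. Sensitivity to loss.** Assuming that period 1 alone lost as much as 20% (16 per group), power is 0.19 two-sided or 0.28 one-sided.

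**The case against.** The strongest reply is that the analysis is an ANCOVA and the sidedness is open, so a single unadjusted two-sided figure is unfair. Much of that stands. A reader might infer that power is simply 0.24 and the miss rate 76%. The article does not support fixing on that figure, because its hypothesis is directional and its own N = 32 fits a one-sided 0.025; the range 0.24 to 0.34 has to be carried. Nor can it be said that adjustment could never reach 0.60. It could, at the correlations shown above. But none is stated, the power sentence lists only alpha and effect size, and 0.50 is already scaled by an SD of change, so only correlation between baseline and change would help.

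Three further inferences are tempting and go too far:

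- **That only 16 per group would be available.** The 20% allowance covers drop-out and protocol deviation over the whole trial, and children lost only in period 2 still contribute to period 1.
- **That the fallback is likely to be used because effects are expected to persist through the break.** Persistence is not differential carryover. A new baseline is taken before period 2, the trigger is a joint condition, and a GEE model with a differential carryover term comes before this analysis.
- **That the first-period analysis should lose its place in the plan.** A wrong power figure does not establish that.

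It is also fair to say that the article already presents this comparison as falling short of its 0.80 target, and that the small/medium mismatch is cosmetic, since no calculation depends on the word.

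**Conclusion.** The point holds as an error of arithmetic. On the stated inputs, the stated power is about 1.8 times (0.60/0.34) to 2.5 times (0.60/0.24) the value obtained. The chance of missing the assumed effect is about 66% (one-sided) to 76% (two-sided). This rests on a 1:1 comparison of independent groups, all 20 per group analysed, and no gain from the covariate; a gain large enough to rescue 0.60 would need a strong correlation that the article does not claim. The correction should be made, but it is not critical: the figure belongs to a conditional third analysis, did not set the sample size, and does not enter the primary analysis or its significance threshold.

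**What to change.** In Analyses, replace 0.60 with the figure for the intended test: about 0.24 if alpha = 0.025 is two-sided, or about 0.34 if it is one-sided. State the sidedness, and keep it consistent with the calculation behind N = 32. If a gain from baseline adjustment is to be claimed, give the assumed baseline-to-change correlation and the resulting power; at r = 0.5, for example, 0.32 two-sided or 0.43 one-sided. Any allowance for loss in period 1 should be labelled as an assumption. Add that the first-period estimate will be reported with its confidence interval, so that a non-significant result is not read as no difference. One label for the 3/6 effect size would tidy the text.

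The cost is a sentence or two and a less favourable figure. Design, sample size, conduct and the role of the first-period analysis can stay as they are.
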